***Characteristics/covariates***			
Pregnancies	Number	Mean/Median	Baseline
Preeclampsia	Yes/No	Mean/Median	Baseline
Chorioamnionitis	Yes/No	Mean/Median	Baseline
Infection pregnancy	Number of infections	Sum	Baseline
Antibiotics during pregnancy	Period	Sum	Baseline
Mode of delivery	Vaginal or Cesarean-section	Mean/Median	Baseline
Apgar-score	At 1, 5 and 10 minutes	Mean/Median, Sum	Baseline
Gender (x/y)	Boy/girl	Mean/Median	Baseline
Multiple birth	Yes/No	Mean/Median	Baseline
Gestational age	Number (gestation week)	Mean/Median	Baseline
Birth weight	Kilograms	Mean/Median	Baseline
Birth length	Centimeters	Mean/Median	Baseline
Birth head circumference	Centimeters	Mean/Median	Baseline
Z-scores from growth chart at birth	Reference Niklasson [73] and Fenton [74]	Standard deviation	Baseline
Respiratory support Intubation	Period of treatment	Mean/Median	From birth until 40 weeks of gestational age
Respiratory support Continuous positive airway pressure (CPAP)	Period of treatment	Mean/Median	From birth until 40 weeks of gestational age
Respiratory support High-flow nasal cannula	Period of treatment	Mean/Median	From birth until 40 weeks of gestational age
Respiratory support Low-flow nasal cannula	Period of treatment	Mean/Median	From birth until 40 weeks of gestational age
Patent ductus arteriosus closure strategies Paracetamol	Period of treatment	Mean/Median	From birth until 40 weeks of gestational age
Patent ductus arteriosus closure strategies Operation	Date	Mean/Median, Sum	From birth until 40 weeks of gestational age

^a^See definition of Bell Stage >II-III under “Plans for assessment and collection of outcomes {18a}”

^b^See definition of verified late-onset sepsis under “Plans for assessment and collection of outcomes {18a}”

### Participant timeline {13}

Table 2 provides an overview of the timeline including enrolment, intervention, and follow-up.

**Table 2 Tab2:**
[figure not shown]
Participant timeline with checkpoints and outcome assessment during enrollment, intervention, and follow-up

*Gestational week

**Corrected age

Figure 1 also provides a flowchart of enrollment, intervention, outcome reporting, and follow-up. It also depicts the participant timeline for main cohort and sub-cohort, including providing details on consent, randomization, intervention, and primary and secondary outcomes for intervention period and during follow-up.

**Fig. 1 Fig1:**
[figure not shown]
Flowchart of enrollment, intervention, outcome reporting, and follow-up

#### Participant timeline for the sub cohort

The follow-up variables for the sub-cohort consist of anthropometric measurements at term, 3 months of age corrected for prematurity, 12 months of age corrected for prematurity, 2.5 years of age corrected for prematurity, 5.5 years of chronological age, and one body composition measurement at 3 months of age corrected for prematurity. Most infants within the sub-cohort will be followed up at the neonatal ward at Karolinska University Hospital, Sweden. If the child is not living in the Stockholm Region at follow-up, body composition will not be assessed. Growth data from the SNQ registry will still be obtained.

### Sample size {14}

The sample size calculation is based on the Swedish average incidence of NEC and mortality in extremely preterm infants, which is comparable for Denmark. During the first two to three postnatal days before the intervention is started, the mortality rate is highest among extremely preterm infants. We will calculate the mortality rate from the start of the third postnatal day, as this is the estimated time the enrolled infants will be exposed to the intervention. Based on pooled incidence rate data from SNQ data from the years of 2019, 2020, and 2021, we considered an 18% base rate of the composite outcome NEC and/or mortality, with an estimated 9% overlap. We estimated a 30% reduction, as this was considered clinically relevant and was also the NEC risk reduction rate seen in the ProPrems trial [6]. After analyzing the relative risk for the power analysis, assuming a significance level of 0.05 and 30% reduction rate with interim analysis based on a Pocock boundary at 1/3, 2/3s, and 100% of the information, the proposed enrollment of 1620 patients will have sufficient power [7] to test our hypotheses. Patient enrollment will continue until this number has been reached. Assuming an 80% consent rate, we expect to enroll 1620 infants in 3 years and 8 months.

### Recruitment {15}

To ensure adequate participant enrollment, it will be possible to enroll patients antenatally as this will ease planning of the enrollment process. Moreover, the enrollment is not only restricted to clinicians but can also be performed by trained study nurses.

To ensure that legal guardians with native languages other than Swedish understand the full extent of the trial, written consent will be available in at least seven languages (Swedish, Danish, English, Arabic, Persian, Somali and Russian). Use of a translator is recommended when needed.

## Assignment of interventions: allocation

### Sequence generation {16a}

Randomization will be done within 24 h after written consent has been obtained from the legal guardians. Allocation to either intervention or control group will be made using the randomization software, *Randomize.net*. The randomization will be stratified by center and the patient will be allocated to either group C or group D.

### Concealment mechanism {16b}

All participating hospitals will have two boxes clearly labeled as “C” and “D,” one containing probiotic sachets and one containing placebo sachets. All researchers, legal guardians, and bedside medical and nursing personnel will not know whether group C or D is receiving the probiotic supplement. The probiotic and placebo sachets are only distinguishable from one another due to being labeled with two different four-digit batch number sequences which will change with every new batch produced. Only the manufacturer of the study product and the Data Safety and Monitoring Committee (DSMC) will have insight regarding group allocation specific to these batch numbers.

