### Criteria for discontinuing or modifying the allocated interventions {11b}

The supplementation of probiotics (intervention) or placebo (control) will be administered in the same manner as given in the ProPrems trial [12] and according to existing clinical routines previously mentioned for infants born after gestational week 28 in Swedish hospitals. Variation in the timing of the administration of the intervention is acceptable if local clinical routines for probiotic supplementation are already set. As the probiotic mixture has been reported to remain stable for 4 h, the intervention must be given within 4 h [70]. Otherwise, a new mixture must be prepared.

All researchers, medical, and nursing staff will be blinded until the final analysis has been performed. However, code breaking will occur in connection to a suspected unexpected serious adverse reaction (SUSAR) due to the seriousness of the situation.

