### Procedure for unblinding if needed {17b}

Only the DSMC will have access to the code for blinding/unblinding. In addition, a code breaking list will be stored in a locked cabinet or equivalent and only accessible to the main PI at the central study center (Karolinska University Hospital). In case of an emergency where access to the code breaking information is required, the main PI may initiate code breaking.

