### Data management {19}

Data will be collected and maintained with the electronic data capture application, REDCap. REDCap is a secure web platform for building and managing online databases and surveys. Data will be accessible for all research group members but not to unauthorized personnel. Members of the research team at every site will only have access to data from their own hospital. The PI and other members from the main research group at Karolinska will have access to data collected at all hospitals. All researchers will be blinded during the study and analyses.

REDCap will be accessible to all university hospitals taking part in the research project. The software enables very robust traceability of the research output, including an audit trail that traces data entry and editing. Access to what data can be viewed and modified can be customized for each person within the research project. The data is stored automatically at two different servers around Stockholm which are backed up every hour. Data will be analyzed using the statistical analysis software, STATA.

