#### Reporting SUSARs

Investigators are required to report SUSARs to the main PI as soon as possible and no later than 24 h following the incident. The initial report must be made by phone.

A complementary written report must be completed immediately using the data collection instrument in REDCap entitled, “reporting of SUSAR.”

In the event of code breaking in connection to a SUSAR, blinding must still be preserved during the ongoing trial. The oral or written report should therefore not contain information about regarding whether the patient was receiving the probiotic supplement or not.

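### Two trial-wide letters carry the blind, the sections disagree on who holds their key, and the main PI and central group can see letters alongside outcomes

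*Protocol article*

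**What the plan says.** **Letters.** Under Sequence generation {16a}, randomization is stratified by center and "the patient will be allocated to either group C or group D". Concealment mechanism {16b} adds: "All participating hospitals will have two boxes clearly labeled as" C and D, "one containing probiotic sachets and one containing placebo sachets". Batch numbers change with each production run, but the box letters do not. Implementation {16c} uses a binary code for data collection and analysis, and Who will be blinded {17a} defines blinding as not knowing which of the two letters is the probiotic.

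**Key.** Concealment mechanism {16b}: "Only the manufacturer of the study product and the Data Safety and Monitoring Committee (DSMC) will have insight regarding group allocation" tied to the batch numbers. Procedure for unblinding {17b} first limits the code to the DSMC, then adds that "a code breaking list will be stored in a locked cabinet or equivalent and only accessible to the main PI" at Karolinska, who may initiate code breaking in an emergency. The discontinuation section {11b}, Who will be blinded {17a} and Data management {19} all describe researchers as blinded.

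**SUSARs.** Section {11b} states that "code breaking will occur in connection to a suspected unexpected serious adverse reaction (SUSAR"). Reporting SUSARs sends the first report to the main PI and requires: "In the event of code breaking in connection to a SUSAR, blinding must still be preserved during the ongoing trial". Its only stated means is to leave the treatment out of the report.

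**Access.** Group assignment is an eCRF variable ({18a}), and the identification log carries the letter ({27}). Validation of NEC and late-onset sepsis (LOS) is documented in REDCap ({18a}), and SAEs, which include death, go into the eCRF. "The PI and other members from the main research group at Karolinska will have access to data collected at all hospitals" ({19}), and the same people can open all identification logs ({27}).

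**The concern.** With two letters and one meaning, the blind of the whole trial is a single binary fact. Whoever learns it, by a code break or by inference, can read the arm of every past and future infant whose letter is visible to them. With infant-specific codes, one break would reveal one infant.

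The person best placed to learn it is the main PI, who holds the list, may start a code break, receives every SUSAR report and sees all hospitals' letters and data. The protocol calls that same person blinded. The central group lacks the list but can set letters beside outcomes while recruitment continues.

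At stake are the judgement-dependent steps: work-up, diagnosis, validation, and advice given to sites. Site PIs oversee allocation to C or D and also validate NEC and LOS, so the validators know the letter and lack only its meaning.

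**Working it through.** The protocol states no figure on this point, so there is none to reproduce. The check sets the sections side by side and then sizes two routes to the key.

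**1. Do the letters mean the same at every site?** No sentence says so outright. The wording is singular in {16b} and {17a}, there is one binary code in {16c}, and all hospitals use the same two labels. No other reading is natural.

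**2. Who holds the key?**
- {16b}: manufacturer and DSMC only.
- {17b}, first sentence: DSMC only.
- {17b}, second sentence: also a list for the main PI.
- {11b}, {17a}, {19}: all researchers blinded.

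These statements cannot all stand as worded.

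**3. Can letter and outcome be joined during the trial?** Yes, for the main PI and central group. The letter is in the eCRF and the log, NEC/LOS validation and SAEs are in REDCap, and access covers all hospitals. Teams at other sites see only their own hospital's data.

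**4. What would the joined data show?** Inputs from Sample size {14}: 18% base rate and 30% relative reduction, so 0.18 × 0.70 = 12.6%. Equal allocation ({8}) gives n infants per letter. Under the normal approximation, the probability that the letter with fewer events is the probiotic is Φ(z), with

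z = (0.18 − 0.126) / √[(0.18×0.82 + 0.126×0.874)/n] = 0.054 / √(0.2577/n)

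| Infants in total | n per letter | Expected events | z | Probability |
|---|---|---|---|---|
| 540 | 270 | 48.6 vs 34.0 | 1.75 | 96% |
| 1080 | 540 | 97.2 vs 68.0 | 2.47 | 99% |
| 1620 | 810 | 145.8 vs 102.1 | 3.03 | 99.9% |

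This holds only if the assumed effect is real and the outcomes are complete. With no effect the guess is right half the time, though a wrong belief about the letters can also bias assessment.

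**5. How likely is a formal break?** The protocol gives no SUSAR or code-break rate. With an assumed rate p per infant, P(at least one) = 1 − (1 − p)^1620:

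| Assumed p | P(at least one break) |
|---|---|
| 0.01% | 15% |
| 0.05% | 56% |
| 0.1% | 80% |
| 0.5% | over 99% |

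The common neonatal complications are listed as expected SAEs and so are not SUSARs by default, which favors the lower rates.

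**6. Which outcomes are exposed?** Death is objective. All NEC cases go to an external group of at least two neonatologists and a radiologist, and validation precedes unblinding ({18a}). That group reviews cases put before it, so some risk in which cases are identified remains. LOS is validated by the site PI alone. The analysis is limited to culture-proven LOS ({18a}), which narrows the judgement, but the decision to take a culture remains.

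**The case against.** The best defense is that a code break harms only those who learn the result and can see letters. SUSARs go to the DSMC for investigation, and the DSMC already has the code. If the decode stays there, no blinded person learns anything. The main PI's list is an emergency provision in a locked cabinet, and holding a list is not the same as having read it. The statement in {16b} concerns the batch-number key, which the manufacturer must know. Outcomes come mainly from the registries, and the text does not describe anyone comparing C with D.

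Much of this stands, and it rules out several stronger readings that a reader might infer:
- **That the first SUSAR unblinds the whole trial, so the requirement to preserve blinding cannot be met.** It can be met if the decode stays with the DSMC. Section {11b} does not say that every SUSAR leads to a break, and Reporting SUSARs is worded conditionally.
- **That consent is influenced.** Written consent precedes randomization, and knowing what C means does not reveal the next infant's letter.
- **That the result could not be called double-blind.** The external NEC review and the objectivity of death protect the primary outcome to a large degree.
- **That a break is close to certain.** This depends wholly on an assumed rate.

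What the defense does not remove is that {17b} places a list with a member of the trial team whom other sections call blinded, and that nothing in the text keeps the decode from that person. Leaving the treatment out of a report limits its spread but does not re-blind someone who has learned it. Nor does any section separate the letter from the outcome data for the central group.

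**Conclusion.** The point holds as an inconsistency over who has the key, combined with avoidable access to letters and outcomes together. It should be corrected, but it does not invalidate the trial. A leak of the key can reach up to all 1620 infants for someone with central access, and only the infants at one hospital for a site team. Under the design effect, the event counts alone would point to the right letter with about 96% probability at 540 infants. The chance of a formal break runs from about 15% to over 99% across assumed rates of 0.01% to 0.5% per infant, and the conclusion does not rest on it. The consequence is greatest for LOS and smaller for the composite of NEC and death. The verdict assumes that the letters have one meaning across sites and that REDCap rights are set as the access sections describe.

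**What to change.** 1. **Reconcile the sections.** Align {11b}, {16b}, {17a}, {17b}, {19} and Reporting SUSARs so that, on the trial side, the key and any SUSAR decode are held only by the DSMC or another holder independent of the trial team. Keep an emergency access route through that holder. State that the decode is not passed to the main PI or the central group.

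2. **Restrict the C/D field.** REDCap rights can be set per person ({19}). Until database lock, hide the letter in the eCRF and the identification log from the central research group, and from those validating NEC and LOS wherever they do not need it to dispense product. Hiding it from every research role would not work, because sites need it to pick the right box.

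**Cost.** The first change is wording plus an agreement with the holder, and it makes the emergency route less direct. The second adds a little access administration.

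**Optional.** Several codes per arm from a later batch would limit what one break reveals; eight codes would mean about 1620/8 ≈ 203 infants if used from the start. The logistic cost is real: relabelling by the manufacturer, more boxes at ten hospitals and the satellite hospitals, and a change in the randomization software. Infants already labelled C or D would gain nothing.

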### Implementation {16c}

After the legal guardians have given written consent to clinicians or study nurses, the infant will be randomly assigned to the intervention or control group. The PI at each study center will oversee group allocation via the randomization software, Randomize.net, but this may also be delegated to other research personnel. Data collection and analysis will be made using a binary treatment code to ensure continued blinding of all patients until the completion of the study.

## Assignment of interventions: blinding

### Who will be blinded {17a}

All researchers, legal guardians, and bedside medical and nursing personnel will be blinded, meaning they will not know whether group C or D receives the probiotic supplement.

### Procedure for unblinding if needed {17b}

Only the DSMC will have access to the code for blinding/unblinding. In addition, a code breaking list will be stored in a locked cabinet or equivalent and only accessible to the main PI at the central study center (Karolinska University Hospital). In case of an emergency where access to the code breaking information is required, the main PI may initiate code breaking.

## Data collection and management

### Plans for assessment and collection of outcomes {18a}

Outcome variables will mainly be collected from SNQ for the Swedish NICUs and from the Danish Newborn Quality Database (DNQD) for the Danish NICUs. Data not collected from the registries will be retrieved from patient records and collected in an electronic case report form (eCRF) documented in the electronic data capture application, REDCap. A complete list of data that will be documented in REDCap is found in Additional file 1.

The following variables will be documented in the eCRF:Date of randomizationGroup assignmentDate of start of interventionDate of pause of interventionInfection during pregnancyAntenatal antibioticsIf stool samples were taken (at baseline, 14 days post menstrual age (PMA), 34 weeks PMA, and 12 months corrected age)

Only verified NEC and culture-proven LOS will be used for the analysis. For NEC, this is defined as Bell Stage II-III; Bell Stage I will not be considered. Patient records will be used to exclude or add potential NEC (Bell Stage II-III) as a compliment to the SNQ and DNQ registry. The PI of each site is responsible for validating NEC and LOS diagnoses. All validation of NEC and LOS diagnoses will be made prior to unblinding at the end of study period. Validation will be documented in REDCap. All cases of NEC will be reviewed by an external expert group not involved as a researcher in the PEPS trial. This group will consist of at least two experienced neonatologists and one radiologist.

#### Diagnostic/validation of NEC

Only Bell stage II-III NEC [71] will be counted as a NEC case and considered in the analyses. Bell stage II involves clinical abdominal symptoms and radiological findings. Stage III includes the findings in stage II in addition to severe clinical condition, such as need of intubation and/or need for surgery. NEC validation must include the following:Abdominal symptoms in connection to NEC episodeRadiological findingsPossible differential diagnosesAbdominal surgery

#### Diagnostic/validation of LOS

LOS is defined as culture-proven sepsis via blood and/or urine culture and/or significant clinical impairment and laboratory inflammatory response, where at least one of the following must be confirmed:Leucocytes (LPK) < 5 or > 20 (×10^9^ cells/L)Thrombocytes (TPK) < 100 (×10^9^ cells/L)C-reactive protein (CRP) > 15 mg/L

#### Data collection and assessment for sub-cohort

Data on postnatal growth (Table 3) during the intervention period will be registered as per clinical routine in the nutritional calculation software, Nutrium (nutrium.se). All growth data from the intervention period will be retrieved from Nutrium. Growth data during long-term follow-up will be collected from SNQ and/or medical records (sub-cohort).

**Table 3 Tab3:** Description of outcomes with analysis metric, aggregation method, and time points in sub-cohort

Outcome variables sub cohort			
*Outcome variables - feeding tolerance*	*Analysis metrics*	*Method of aggregation*	*Time point*
Enteral nutrition	Number of days until full enteral feeds	Mean/Median	During study intervention (until 34 weeks of gestational age)
Parental nutrition	Number of days with parental nutrition	Mean/Median	During study intervention (until 34 weeks of gestational age)
Interruptions of enteral nutrition	Number of enteral nutrition interruptions >8 h	Mean/Median	During study intervention (until 34 weeks of gestational age)
Enteral nutrition decreased due to clinical instability	Number of EN decrease >50%	Mean/Median	During study intervention (until 34 weeks of gestational age)
Use of breastmilk fortifiers	Number of days until breastmilk fortifiers is induced	Mean/Median	During study intervention (until 34 weeks of gestational age)
Feeding tube requirement	Number of days requiring a feeding tube	Mean/Median	During study intervention and until 40 weeks of gestational age
Macronutrient intake	Amount of macronutrients given (kcal/kg/day)	Mean/Median	During study intervention (until 34 weeks of gestational age)
Micronutrient intake	Amount of micronutrients given (μg or mg/kg/day)	Mean/Median	During study intervention (until 34 weeks of gestational age)

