## Risk of morbidity and mortality (complete cohort)

### Pathogenesis of NEC

Despite considerable investigative research to date, the pathogenesis of NEC is not well understood. The nature of the disease is widely accepted to be multifactorial, particularly owing to the general immaturity of the gastrointestinal system, namely the intestinal mucosa barrier function. This lack of robustness from the immature gastrointestinal system, alongside the disarray caused by the infiltration of pathogenic bacterial species and exposure to harmful ischemic events, is proposed to instigate the development of NEC [3, 4, 29]. The considerably higher rates of NEC in premature infants compared to those born at term are further evidence for the role of immaturity and disarray in this disease. Several studies have also postulated that the routine use of prophylactic antibiotics in this population negatively impacts the diversity of the microbiome, rendering infants more vulnerable to the overgrowth of harmful bacteria species and eventual NEC development [30–32]. This highlights the immense potential for prevention through strengthening the diversity of the microbiome via probiotic administration.

The current conservative treatment for NEC is bowel rest through parental nutrition and administration of antibiotics for approximately 10 to 14 days. Gastrointestinal surgery is required in up to 50% of cases [3]. Infants surviving NEC may be subject to long-term adverse effects and complications, such as impaired growth, intestinal strictures, or even short-gut syndrome [33, 34]. These drastic treatment measures and considerable risk of morbidity highlight the necessity of further research into preventing NEC.

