## Methods: participants, interventions, and outcomes

### Study setting {9}

We will include 1620 extremely preterm infants at gestational age 22 weeks + 0 days to 27 weeks + 6 days. The infants will be recruited between approximately December 2022 and July 2026 or until enough participants have been included.

Infants will be recruited at six university hospitals in Sweden (Karolinska University Hospital, Skåne University Hospital, Sahlgrenska University Hospital, Linköping University Hospital, Uppsala Univesity Hospital, and Umeå University Hospital), and four university hospitals in Denmark (Rigshospitalet Copenhagen/Glostrup, Aarhus University Hospital, Aalborg University Hospital, and Odense University Hospital).

A sub-study conducted on the sub-cohort will be performed to assess feeding tolerance and postnatal growth. Infants recruited at Karolinska University Hospital will be included in this extended analysis.

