***Characteristics/covariates***			
Use of medical steroids	Period of treatment	Mean/Median	From birth until 5.5 years of age
Use of tetracyclines	Period of treatment	Mean/Median	From birth until 5.5 years of age
Type of enteral nutrition mothers’ own milk, donated breastmilk, formula	Percentages (%)	Proportion	During study intervention (until 34 weeks of gestational age)
Breastmilk fortification	Type	Proportion	During study intervention (until 34 weeks of gestational age)
Breastfeeding at discharge	Full, partly, none	Proportion	Discharge from neonatal intensive care unit/homecare

Daily nutritional assessment of enteral and parenteral nutrition during the intervention period will be documented in Nutrium. These assessments include all macro- and micronutrient intake including type, amount, and strategy of enteral and parenteral feeds. Data on breastmilk fortification and interruptions of enteral feeds will also be documented and collected from Nutrium.

Assessment of body composition will be made at 3 months corrected age using air displacement plethysmography (PeaPod). This is considered “the gold standard” for measuring body composition, including fat, fat-free mass, and bone density, for infants weighing below 8 kg [72]. It applies whole-body plethysmography which is a fast, reliable, and non-invasive assessment. Assessment of body composition will be documented and retrieved from patient records.

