#### Tertiary aims 1–2

The effect on feeding tolerance (tertiary aim 1) and postnatal growth (tertiary aim 2) will be analyzed using standardized logistic regression and linear regression models.

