### Methods in analysis to handle protocol non-adherence and any statistical methods to handle missing data {20c}

A per-protocol analysis accounting for non-compliance will be performed. Despite this, there is no anticipation of a significant degree of non-adherence and/or missing data, as the intervention will only be carried out during hospitalization and most outcome data after discharge will be generated from the SNQ and DNQD registry. If data is missing from a registry extract, patient records will be searched to complete data collection.

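### Days to full enteral feeds and days to fortifier start have no value for infants who die first or miss the milestone by 34 weeks, so linear regression on the count cannot cover all randomised sub-cohort infants

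*Protocol article*

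**What the plan says.** All references are to the protocol article.

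- **Metric and window.** Table 3 (Data collection and assessment for sub-cohort) lists "Number of days until full enteral feeds" and "Number of days until breastmilk fortifiers is induced" among the feeding-tolerance outcomes. Both are summarised as mean/median, and both are observed during the intervention, which ends at 34 weeks.
- **Model.** Under Tertiary aims 1–2, the effects on feeding tolerance and on postnatal growth "will be analyzed using standardized logistic regression and linear regression models". The sentence does not assign a model to each outcome.
- **Data source.** In the text after Table 3: "Daily nutritional assessment of enteral and parenteral nutrition during the intervention period will be documented in Nutrium". A milestone reached after 34 weeks is therefore not part of the planned nutritional record.
- **Population.** Section {9} enrols infants at "gestational age 22 weeks + 0 days to 27 weeks + 6 days". Section {20a} analyses the data by intention to treat and per protocol, and reports the primary analysis by intention to treat.
- **Missing data.** Section {20c} states that "there is no anticipation of a significant degree of non-adherence and/or missing data". Its only remedy is to search patient records when a registry extract is incomplete.

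The article contains no censoring rule, assigned value, ranking or time-to-event method for an infant without the milestone.

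**The concern.** A count of days to a milestone exists only for infants who reach it while observed. An infant who dies before full feeds, or is alive at 34 weeks without full feeds, has no number to enter. A record search cannot supply one, because the event did not happen in the window. Regression software then leaves the infant out unless the analyst assigns a value, such as the length of the window.

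Either choice matters because loss of the value is not random with respect to treatment. The article describes NEC treatment as "bowel rest through parental nutrition and administration of antibiotics for approximately 10 to 14 days", says surgery is needed in up to half of cases, and plans the main trial on 18% of controls having NEC and/or death. These events delay or prevent full feeds, and they are what the product is meant to reduce. If it works, more placebo than probiotic infants would lack a value. Infants with a count are then a group selected after randomisation, and the estimate for tertiary aim 1 is not a comparison of the arms as randomised.

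**Working it through.** **1. Plan's own figure.** The article gives no expected mean, SD, effect or non-attainment rate for these outcomes, so there is nothing to reproduce. The main-trial size of 1620 does not enter the argument.

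**2. Length of the window**, counting from birth (the article does not state the origin of the count):

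- Born at 22+0: 34×7 − 22×7 = 238 − 154 = 84 days.
- Born at 27+6: 238 − (27×7 + 6) = 238 − 195 = 43 days.

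An infant born at 27+6 who needs 45 days is lost, while one born at 22+0 who needs 80 days is kept. The infants without a value are therefore not simply the slowest feeders.

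**3. Simulation A: delay caused by the composite event.** From the article: 18% events on control and 18% × 0.7 = 12.6% on probiotic, and the window above. Assumed: gestational age uniform over 22–28 weeks; time to full feeds normal with mean 20 (SD 8) or 25 (SD 10) days, floor 5; a 2-day direct benefit; 400,000 infants per arm. Loss = 1 − (difference in attainers ÷ difference in all infants).

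| Assumption for event infants | No value, placebo | Loss of effect |
|---|---|---|
| Delay of 12–14 days (SD 4), near the article's 10–14 days of bowel rest | 0.3–1.6% | about 2–6% |
| Delay of 28 days (SD 10) | 3.7–5.8% | 15–22% |
| Same delay, and 50–100% forced never to attain | 11–18% | about 27–45% |

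For the second row: 1 − 2.89/3.40 = 15% and 1 − 2.73/3.49 = 22%. Without a direct effect, the 28-day delay alone makes an indirect benefit of about 1.5 days. Attainers show 1.1 to 0.96 days of it, or 0.6 to 0.0 days if 50–100% of event infants never attain.

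**4. Simulation B: uniform 15% shortening, no deaths.** All feeding inputs are assumed: time to full feeds is lognormal and longer at lower gestational age, with 1,000,000 infants per scenario.

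| Non-attainment, control / probiotic | Difference, all infants (days) | Attainers only | Loss | Capped at window end | Median difference, non-attainers ranked worst |
|---|---|---|---|---|---|
| 0.4% / 0.1% | 2.91 | 2.78 | 4% | 2.88 | 2.57 |
| 4.8% / 2.6% | 3.89 | 2.68 | 31% | 3.41 | 3.15 |
| 13.3% / 8.9% | 5.13 | 2.31 | 55% | 3.55 | 3.93 |

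Capping at the window end attenuates less than exclusion but does not remove the problem: 1 − 3.41/3.89 = 12% and 1 − 3.55/5.13 = 31%. The median with non-attainers ranked worst is a different estimand, so it need not match the mean difference, but it can be estimated in every scenario.

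**5. Direction.** Using the model of Simulation B:

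- Benefit confined to easier feeders, 13.3% non-attainment in both arms: attainers give 2.49 days against 2.09 in all infants, an overstatement.
- Deaths before full feeds doubled on probiotic: 3.21 against 2.90 days, an overstatement.
- No feeding effect but 30% fewer deaths on probiotic: a spurious harm of about 0.15 day.

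**The case against.** The strongest reply is that the article never says these infants are dropped. Its sentence on models covers every tertiary outcome and names logistic as well as linear regression, so full feeds by 34 weeks could be analysed as yes or no. Table 3 allows a median, which can be estimated with non-attainers ranked last. How to code such infants in a tertiary outcome is ordinary content of an analysis plan that is not shown. The outcome is one of several feeding measures at one centre, and days of parenteral nutrition and feeding interruptions can be counted without the milestone.

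Part of this stands. Exclusion is what software does with a missing value, not a rule in the article, and the stakes are limited. What does not stand is that the matter is merely left open. The article fixes a day-count metric, a closing date and regression models, and a day count goes to the linear model unless it is dichotomised. Those choices together cannot include every randomised sub-cohort infant.

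A reader might go further and infer that the worst feeders are certain to be dropped, that a benefit is certain to be understated, and that about a third or more of it would be lost. The documents do not support this. The window varies with gestational age, the direction can reverse, and losses of 27–45% in Simulation A appear only when half or all of event infants are assumed never to reach full feeds. No figure in the article supports that assumption. Simulation A also gives infants who die a notional feeding time and places every event before full feeds, both of which are simplifications.

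**Conclusion.** The point holds in a limited form. For both milestone outcomes, linear regression on the count would exclude infants who die or do not attain by 34 weeks, or would need an arbitrary value for them, and their absence is related to events the product is meant to change. Understatement of a benefit is the usual direction but is not guaranteed.

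The size rests on an unstated non-attainment rate. Across the two sets of assumptions with a direct feeding benefit, the loss is a few percent when about 1% or fewer control infants lack a value, about 15–30% at about 4–6%, and about 27–55% at 11–18%. These are illustrations, not forecasts. The change should be made because it is cheap and the bias could not be judged from attainers alone. It affects tertiary aim 1 at one centre and leaves the primary conclusion untouched.

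**What to change.** For days to full enteral feeds and days to fortifier start:

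- State the time origin, and analyse both as time to event in all randomised sub-cohort infants.
- Censor infants alive without the milestone at 34 weeks, and treat death as a competing event.
- Adjust for gestational age, because it determines the censoring time as well as the pace of feeding.
- Report cumulative incidence by arm, with a subdistribution hazard ratio or the difference at a fixed day. Counted from birth, every infant has a window of at least 43 days, so a day no later than that avoids censoring by the window. A median with non-attainers and deaths ranked worst is an acceptable alternative.
- Report the numbers not attaining and dying before the milestone by arm.
- Do not use linear regression on attainers only.

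The cost is analysis wording, settled before unblinding. Daily nutrition during the intervention is already to be recorded, so no new data are needed. The drawback is that the effect is no longer a simple mean difference in days.
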